# The optimized acupuncture treatment for neck pain caused by cervical spondylosis: a study protocol of a multicentre randomized controlled trial

**DOI:** 10.1186/1745-6215-13-107

**Published:** 2012-07-09

**Keywords:** Acupuncture, Cervical spondylosis, Neck pain

## Abstract

**Background:**

Neck pain is one of the chief symptoms of cervical spondylosis (CS). Acupuncture is a well-accepted and widely used complementary therapy for the management of neck pain caused by CS. In this paper, we present a randomized controlled trial protocol evaluating the use of acupuncture for CS neck pain, comparing the effects of the optimized acupuncture therapy in real practice compared with sham and shallow acupuncture.

**Methods/Design:**

This trial uses a multicentre, parallel-group, randomized, sham acupuncture and shallow acupuncture, controlled single-blind design. Nine hospitals are involved as trial centres. 945 patients who meet inclusion criteria are randomly assigned to receive optimized acupuncture therapy, sham acupuncture or shallow acupuncture by a computerized central randomization system. The interventions past for 4 weeks with eight to ten treatments in total. The group allocations and interventions are concealed to patients and statisticians. The Northwick Park Neck Pain Questionnaire (NPQ) is used as the primary outcome measure, and the McGill Pain Questionnaire (MPQ) and The Short Form (36) Health Survey (SF-36) are applied as secondary outcome measures. The evaluation is performed at baseline, at the end of the intervention, and at the end of the first month and the third month during follow-up. The statistical analyses will include baseline data comparison and repeated measures of analysis of variance (ANOVA) for primary and secondary outcomes of group and time differences. Adverse events (AEs) will be reported if they occur.

**Discussion:**

This trial is a multicentre randomized control trial (RCT) on the efficacy of acupuncture for CS neck pain and has a large sample size and central randomization in China. It will strictly follow the CONSORT statement and STRICTA extension guideline to report high-quality study results. By setting the control groups as sham and shallow acupuncture, this study attempts to reveal the effects of real acupuncture versus placebo or non-classic acupuncture treatment and evaluate whether classic Chinese medical acupuncture is effective on CS neck pain. This study will provide evidence for the effects of acupuncture on CS neck pain.

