Problems in the design of some studies have also been identified. Some trials had a small sample size without the correct calculation of the sample size required to give meaningful statisics [6-8], whereas others lacked a meaningful control group [9] or blinding techniques to prevent subjective bias [10,11]. Therefore, a well-designed, multicentre RCT with sound methods for calculating sample size and establishing a meaningful control group is needed to evaluate the effects of classic Chinese acupuncture for the treatment of CS neck pain.

The current study was designed as a randomized, controlled, single-blind study, covering nine centres and comparing three groups (one treatment group and two control groups).. The sample size was calculated based on the data from a 178-case pilot study [1] and referred to the large-scale pragmatic trial design recommendation proposed by Salter *et al*. [12]. The objective of the trial was to evaluate the effects of optimized acupuncture therapy (OAT) for CS neck pain.

The trial protocol is reported here in accordance with CONSORT 2010 statement [13], and the intervention acupuncture details are described in accordance with the STRICTA 2010 extension [14,15].

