#### The optimized acupuncture therapy group

The treatment scheme for the OAT group consists of traditional acupuncture therapy, followed by intradermal needle therapy (INT). Nine acupuncture points were selected for the OAT group based on the advice and consensus of the national expert committee of acupuncturists detailed above. The name/code and location of the acupuncture points followed the WHO standards where possible [17-19], and are: Jianzhongshu (SI15, bilateral); Dazhui (GV14); Zhongzhu (TE3, bilateral); and Huatuojiaji (extra point; four points in two pairs, bilateral). The Huatuojiaji points are traditional Chinese acupuncture points, but are not listed in the WHO standard. To locate these four points, the acupuncturist needs to identify the cervical positive reaction planes by palpating the area 12.5 mm away from the patient’s cervical vertebra. If any tender points are found, the corresponding cervical vertebra level is considered the cervical positive reaction plane. The four Huatuojiaji points are located at the top ( upper Huatuojiaji) and bottom (lower Huatuojiaji) of th cervical positive reaction plane(s) bilaterally and 12.5 mm horizontally away from the corresponding cervical vertebra. If only one cervical positive reaction plane is identified, the practitioner should select a pair of the Huatuojiaji points on the cervical positive reaction plane and a second pair on the cervical vertebra next to the first pair.

The doctors performing all therapies have at least 5 years of acupuncture experience. Disposable stainless steel needles (0.3 mm × 40 mm; Suzhou Tianxie Acupuncture Instruments Co. Ltd, Su Zhou City, China) are used. The needles are inserted into the muscular tissue of the acupuncture points (to a depth of 20 mm) using the tube-guide method. The inserted needles are manually manipulated until the patient feels numbness or other acupuncture sensation (known as ‘de qi’), and the needles will be retained in the points for 20 minutes.

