#### The sham acupuncture group

Skin-penetrating shallow needles on sham points are used in the sham group. The location of the sham points is defined as 25 mm lateral to the standard location used in the OAT group: the sham point of Dazhui (GV14) is 25 mm vertically below the standard GV 14, the sham points of Jianzhongshu (SI15) and Huatuojiaji are 25 mm lateral to the standard SI15 and the corresponding points of Huatuojiaji, and the sham point of Zhongzhu (TE3) is 25 mm proximal to the standard Zhongzhu (TE3). The same type of disposable stainless-steel needles is used in the sham group as in the OAT group, therefore, the intervention in the sham group cannot be differentiated by needle appearance. The needles (0.22 mm × 40 mm) are inserted into the skin to a depth of 3 mm and remain at the subcutaneous level for 20 minutes. The doctor uses the tube-guide method, and any manipulation for acupuncture sensation or de qi is prohibited.

After sham acupuncture, the patients will be treated by point pressing. The point selection scheme is the same as for the INT in the OAT group. To ensure blinding, Semen Vaccariae (the seeds of the cow cockle, *Vaccaria hispanica*) are used to press on each point to conceal from the patient whether INT is being administered; as the points are all on the back, the patient cannot see what is being pressed on their skin.

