#### The shallow acupuncture group

For the shallow group, the point selectionp is the same as for the OAT group; however, the doctor is required to insert the needles vertically to the subcutaneous level at a depth of no more than 3 mm. Any sensation (de qi) or needle manipulation is prohibited in this group. After acupuncture, the patients will also treated by INT using the same method as in the OAT group.

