## Discussion

The objective of this trial is to evaluate the effect of the OAT scheme for neck pain in patients with CS. The first draft of the OAT treatment scheme was developed based on the practice and clinical experience of the Acupuncture Department of Guangdong Provincial Hospital of Chinese Medicine. The draft was then discussed by a special committee of Guangdong Association of Acupuncture and revised. The revised edition was submitted and reviewed by the national expert committee of acupuncturists organized by SATCM, and the final version of the OAT scheme was approved by the consensus of the committee.

The OAT scheme comprises two steps: the first step is classic acupuncture therapy at the nine standard points with de qi sensation for 20 minutes, and the the second step is the administration of INT in which the needles are fixed by medical tape. The treatment lasts for 4 weeks with eight to ten sessions at a frequency of two to three times per week. The overall effect of OAT is related to the duration and frequency of the treatment. The intradermal needles are an empirical method to maintain the pain-relieving effect of classic acupuncture, therefore, the treatment frequency of classic acupuncture can be reduced to twice per week. As a result, both the final outcome and patient compliance are improved.

For a high-quality RCT, use of the appropriate control is crucial. In this trial, two questions must be addressed. First, is the OAT treatment effective on CS neck pain? Second, does the OAT treatment have a superior effect to the control treatments in treating CS neck pain? The sham and shallow acupuncture groups were designed as control groups in this study to answer these questions.

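### The Abstract promises a verdict on classic acupuncture, but OAT versus sham and the three-group test can support a verdict only on the OAT package

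*Protocol article*

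**What the plan says.** The article describes its aim in two ways.

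- **The package.** The Background gives the formal objective: "The objective of the trial was to evaluate the effects of optimized acupuncture therapy (OAT) for CS neck pain". The main-text Discussion repeats it, and both of its questions concern OAT. The Interventions section hypothesises that OAT will beat both a placebo effect and a non-specific one, and gives this as the reason for two control groups.
- **Classic acupuncture.** The Abstract (Discussion paragraph) sets the trial this task: "reveal the effects of real acupuncture versus placebo or non-classic acupuncture treatment and evaluate whether classic Chinese medical acupuncture is effective on CS neck pain". The Background motivates the trial as one "needed to evaluate the effects of classic Chinese acupuncture for the treatment of CS neck pain".

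The main-text Discussion separates the two ideas. It calls the first step of OAT (nine points, de qi, 20 minutes) classic acupuncture. The second step is intradermal needling, with its own purpose: "The intradermal needles are an empirical method to maintain the pain-relieving effect of classic acupuncture".

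On the control arms, the sham section specifies 3 mm needling at displaced points without de qi, and then: "After sham acupuncture, the patients will be treated by point pressing". The shallow section keeps the OAT points, forbids depth beyond 3 mm and de qi, and adds: "After acupuncture, the patients will also treated by INT using the same method as in the OAT group".

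Statistical analyses specifies a repeated measures ANOVA with treatment as one between-subjects factor.

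**The concern.** By the article's own terms, OAT is classic needling plus something else that is expected to work. The sham arm lacks both. If OAT beats sham, the benefit could come from the classic needling, from needles left in the skin between sessions, or from both. The Abstract's sentence names one of these as the thing the trial will have evaluated.

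At stake is the wording of the conclusion. A report could say that classic acupuncture is effective on the strength of OAT versus sham, or of a significant three-level treatment factor, when the data show only that the package beat the sham package.

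**Working it through.** **Step 1. What each contrast changes** (from the three intervention sections)

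| Feature | OAT | Shallow | Sham |
|---|---|---|---|
| Needling location | standard | standard | displaced 25 mm |
| Depth | 20 mm | at most 3 mm | 3 mm |
| De qi | sought | prohibited | prohibited |
| Second step | intradermal needles | intradermal needles | seed pressing |

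- OAT versus sham changes all four rows.
- OAT versus shallow changes depth and de qi only.
- Shallow versus sham changes needling location and the second step together, so no contrast isolates location.
- No arm gives classic needling without intradermal needles, and none gives sham needling with them.

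**Step 2. Reproduce the planned size** (Sample size calculation)

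Inputs: OAT 20.71 (SD 11.91); both controls 24.04 (SD 11.83); alpha 0.05; power 0.90.

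One-way ANOVA, noncentrality λ = n Σ(mean − grand mean)² / SD². The grand mean is 22.93, so the sum of squares is 2.22² + 1.11² + 1.11² = 7.393. With n = 244 and SD 11.91, λ = 244 × 7.393 / 141.85 = 12.72, and power on 2 and 729 df is 0.900. The planned 244 per group is reproduced.

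**Step 3. Pairwise power when the intradermal step has share s of the gap**

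The documents give no value for s, so the full range is shown. The gap is 24.04 − 20.71 = 3.33. The pooled SD is √((11.91² + 11.83²)/2) = 11.87. At 244 per arm, SE = 11.87 × √(2/244) = 1.075. Power is about Φ(difference/SE − 1.96).

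- OAT versus sham: 3.33/1.075 = 3.10, so power is 0.87. It does not depend on s.
- OAT versus shallow: the difference is 3.33 × (1 − s).

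| s | Difference | OAT v shallow, 244 per arm | 268 per arm |
|---|---|---|---|
| 0% | 3.33 | 0.87 | 0.90 |
| 25% | 2.50 | 0.64 | 0.68 |
| 50% | 1.67 | 0.34 | 0.37 |
| 100% | 0 | 0.05 | 0.05 |

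The 268 column uses the number of completers per arm given in the main-text Discussion. OAT versus sham then has power 0.90.

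**Step 4. The three-group test under the same assumption**

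- s = 0% (the planned pattern): 0.90.
- s = 50% (20.71, 22.375, 24.04): the sum of squares is 2 × 1.665² = 5.544, λ = 9.54, power 0.79.
- s = 100% (20.71, 20.71, 24.04): the sum of squares is again 7.393, power 0.90.

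The three-group test has the same power when classic needling produces the whole gap as when it produces none of it.

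**The case against.** The strongest reply is that the trial never set out to isolate classic needling. The stated objective, the hypothesis and both questions in the main-text Discussion concern OAT, and a package against a sham package is a legitimate design. The Background phrase about classic acupuncture describes what research is needed. It is not the objective. This stands: a reader might infer that the trial cannot answer its main question, and the documents do not support that.

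Second, the shallow arm already guards against the worst case. If the intradermal step did everything, OAT would equal shallow, the hypothesis of beating both controls would fail, and the data would show it. The Abstract names non-classic acupuncture as a comparator, and nowhere does the article say that OAT versus sham is enough. This also stands. What remains is that the Abstract's sentence about classic acupuncture is not linked to the contrast that bears on it.

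Third, the intradermal share is assumed. A reader might infer from the lower rows of the table that the step probably produces half or more of the effect. Nothing in the documents supports that. The sample size calculation gives sham and shallow the same mean, which corresponds to a share of 0%. That is hard to square with the Discussion's reason for using intradermal needles, but it is the plan's assumption. The figures also treat one time point, whereas the analysis is repeated measures.

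Fourth, pairwise comparisons may well be set out in a full protocol or SAP that is not shown. Their absence from the article is not the point here.

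Two further inferences should be resisted. A positive OAT-versus-shallow result would not by itself show that classic acupuncture is effective, because it tests depth with de qi against a control that also has intradermal needles, not against placebo. And although the Background criticises earlier trials for departing from classical points, it does not commit this trial to testing point specificity.

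**Conclusion.** The point holds as a mismatch between one stated conclusion and the contrasts available, not as a fault in the arms or in the formal objective. OAT versus sham is a valid test of the OAT package. Neither it nor the three-group test can attribute benefit to classic needling as the main-text Discussion defines it. OAT versus shallow can speak to part of that question: the added effect of deep needling with de qi when both arms have intradermal needles.

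This conclusion follows from the arm descriptions and needs no assumption about effect size. The power figures illustrate it and rest on the plan's means and SDs, a single-time-point comparison and an assumed intradermal share. They show that a positive OAT-versus-sham result is equally likely at every share (0.87 at 244 per arm), so it carries no information about that share.

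**What to change.** Change wording only:

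1. In the Abstract's Discussion paragraph, state the conclusion as the effect of the OAT package compared with the sham package.
2. In Interventions and the main-text Discussion, name OAT versus shallow as the contrast for the added effect of deep needling with de qi when both arms receive intradermal needles. Make any statement about the classic needling component depend on that contrast, and not on the three-group test or on OAT versus sham.
3. Claim efficacy in the sense of the Interventions hypothesis only if OAT is superior to both controls, and make no claim about point specificity.

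No arm, treatment, patient or data item changes. The cost is a narrower claim if only OAT versus sham is positive.

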**Trial Registration:**

Chinese Clinical Trial Registry: ChiCTR-TRC-00000184.

## Background

Cervical spondylosis (CS) is caused by unspecified degenerative changes of the muscles, tendons, joints, and bones of the neck and shoulder [1]. The main symptom of CS is pain and stiffness in the neck, sometimes accompanied by numbness and radicular pain to the arms and fingers. The overall prevalence of neck pain has been reported [2] as ranging from 0.4% to 86.8% (mean 23.1%). In a high-risk population (office and computer workers), the 1-year incidence of neck pain ranged from 10.4% to 21.3% [2], and most of these cases are empirically determined to be caused by CS (hereafter referred to as CS neck pain).

The management goals for CS neck pain are to diminish pain intensity, facilitate physical neck movement, and restore daily function. Therapies for the disorder include both individual (administration of non-steroidal anti-inflammatory drugs), muscle relaxants, and analgesics [3]), and public (establishment of healthcare policies and the delivery of healthcare advice, physical training and stress management techniques [4]) treatment approaches. However, little evidence is available to support the effectiveness of care at either the public or individual healthcare level [3,4].

Complementary therapies such as acupuncture, massage, neck exercises, mechanical traction, and electrotherapy are well accepted as alternative treatments for CS neck pain. Acupuncture has been extensively used for the management of CS neck pain, and a number of clinical trials have been conducted to test its efficacy. However, the evidence remains moderate, because of defects in study design and in evaluation methods used in current systematic reviews [5].

One problem is that many new acupuncture methods have been introduced in these studies. For example, trigger-point acupuncture was reported to be effective for chronic neck pain in elderly patients [6]. Another study reported that tender-point acupuncture had short-term effects on neck and shoulder pain and stiffness [7]. Traditional acupuncture therapy is based on the classical knowledge of Chinese medicine, and acupuncture point selection should follow those classical principles and specific locations. Thus, the aforementioned studies provide evidence only for the efficacy of needle insertion, not for the efficacy of acupuncture *per se*.

Problems in the design of some studies have also been identified. Some trials had a small sample size without the correct calculation of the sample size required to give meaningful statisics [6-8], whereas others lacked a meaningful control group [9] or blinding techniques to prevent subjective bias [10,11]. Therefore, a well-designed, multicentre RCT with sound methods for calculating sample size and establishing a meaningful control group is needed to evaluate the effects of classic Chinese acupuncture for the treatment of CS neck pain.

The current study was designed as a randomized, controlled, single-blind study, covering nine centres and comparing three groups (one treatment group and two control groups).. The sample size was calculated based on the data from a 178-case pilot study [1] and referred to the large-scale pragmatic trial design recommendation proposed by Salter *et al*. [12]. The objective of the trial was to evaluate the effects of optimized acupuncture therapy (OAT) for CS neck pain.

The trial protocol is reported here in accordance with CONSORT 2010 statement [13], and the intervention acupuncture details are described in accordance with the STRICTA 2010 extension [14,15].

## Methods/Design

### Ethics review and informed consent

The study protocol was reviewed and approved by the Ethics Committee of Guangdong Provincial Hospital of Chinese Medicine (number 2008GL-10),and registered in the Chinese Clinical Trial Registry (number ChiCTR-TRC-00000184), which is a primary registry in the WHO registry network (http://www.chictr.org/). All patients are required to provide informed consent.

### Trial status

Patients are currently being recruited into the study, and the follow-up is being conducted.

### Trial design

The study was designed as a randomized, parallel-group, single-blind trial to evaluate the effects of OAT for CS neck pain. The following nine hospitals located in different regions of China were chosen for involvement in the trial: Guangdong Provincial Hospital of Chinese Medicine, the First Affiliated Hospital of Hunan University of Chinese Medicine, the Secondary Affiliated Hospital of Hunan University of Chinese Medicine, Xinjiang Medical University Affiliated Hospital of Traditional Chinese Medicine, the Third Hospital of Shanxi Institute of Traditional Chinese Medicine, the Second Affiliated Hospital of Guiyang Institute of Traditional Chinese Medicine, the People’s Hospital of Hainan Province, the Second People’s Hospital of Zhaoqing City, and the People’s Hospital of Huizhou City.

### Study procedure and patient recruitment

The study procedure is illustrated in the flow chart in Figure 1.

**Figure 1 F1:**
[figure not shown]
Patient recruitment.

The researchers will distribute trial information leaflets to the outpatient clinics of the hospitals, local communities, and university campuses to recruit potential patients whose major symptoms are neck pain and stiffness. The leaflets contain a brief questionnaire for screening patients with CS and provide contact information for the researcher. The patients are given a physical examination and radiography assessment to confirm the diagnosis of CS, and the protocol details are explained to them. Patients are included only if they meet the inclusion criteria and sign an informed consent document.

#### Inclusion and exclusion criteria

The inclusion criteria for the trial are:

· Age 18 to 60 years (both males and female patients are included).

· A confirmed diagnosis of CS in accordance with the diagnostic criteria published by Chinese Medical Association and referring to the *International Classification of Diseases*, 10th edition (ICD-10) [16] codes: M47.2 (other spondylosis with radiculopathy), M47.8 (other spondylosis → cervical spondylosis), or M47.0 + G99.2* (anterior spinal and vertebral artery compression syndromes).

· Diagnosis of CS supported by a cervical radiographic examination, such as anteroposterior and lateral X-rays, or magnetic resonance imaging/computed tomography scans showing cervical spine degeneration or cervical disc herniation.

· The main symptom of neck pain.

· Episodes of neck pain episodes lasting at least 0.5 hours, and occurring at a frequency of at least once per month for the 3 months prior to study entry.

· Pain intensity of more than 3 points as measured on a visual analog scale (VAS) at the time of recruitment.

· No acupuncture therapy within the 3 months prior to study entry.

The exclusion criteria are:

· Pregnancy or lactation.

· Confirmed diagnosis of spondylogenic compression of the spinal cord referring to the ICD-10 [16] code M47.1 + G99.2*.

· Complications of severe systematic diseases such as diabetes mellitus, cardiocerebrovascular disorders or tumors

· Considered not suitable to participate the trial by the researchers.

· History of neck trauma, cervical fracture or cervical surgery, neurologic impairment (for example, myasthenia or abnormal spinal nerve reflex), or congenital spinal abnormality, or a diagnosis of systemic disease of the bones or joints.

· Duration of neck pain and/or neck stiffness episodes of less than 0.5 hours or history of episodes have occurred over less than < 3 months.

· Rejection or fear of acupuncture therapy.

· Use of any type of acupuncture within the 3 months prior to study entry.

· Use of any other treatments (drug or non-drug).

